## Abstract

**Background:**

Postoperative sore throat (POST) is a common postoperative complication after endotracheal tube removal. There are still no effective preventive methods for POST. The aim of this trial is to confirm whether maintaining intraoperative cuff pressure below the tracheal capillary perfusion pressure could effectively reduce the incidence of POST among patients undergoing gynecological laparoscopic surgery.

**Methods:**

This study is a single-center, randomized, parallel-controlled, superiority trial with a 1:1 allocation ratio. Sixty patients whose age is between 18 and 65 years and scheduled for gynecological laparoscopic surgery will be randomized to the cuff pressure measurement and adjustment (CPMA) group and the only cuff pressure measurement without adjustment group (control group). The primary endpoint is the incidence of sore throat at rest within 24 h after extubation. The secondary endpoints include the incidence of cough, the incidence of hoarseness, the incidence of postoperative nausea and vomiting (PONV), POST, and pain intensity within 24 h after extubation. Blocked randomization will be conducted with a computer-generated central randomization online service. The blind method will be applied to subjects, data collectors, outcome evaluators, and statisticians. Outcome assessments will be performed at 0 h and 24 h post-extubation.

**Discussion:**

This randomized controlled study hypothesizes that cuff pressure is the primary influencing factor of POST. By continuous monitoring of endotracheal tube cuff pressure and maintaining it within the range of 18–22 mmHg compared with only continuous measurement without adjustment, it aims to prove that continuous measurement and adjustment of endotracheal tube cuff pressure could be effective in reducing the incidence of POST in gynecological laparoscopic surgery patients. The result of this study could be used as a reference for future multicenter studies to confirm the effect of cuff pressure on POST and provides a scientific theoretical basis for preventing POST to further support comfort medicine.

**Trial registration:**

Chinese Clinical Trial Registry ChiCTR2200064792. Registered on 18 October 2022. This protocol (version 1.0, 16 March 2022) was approved by the Ethics Committee of Beijing Chaoyang Hospital.

## Background

As one of the problems frequently complained about by patients, postoperative sore throat (POST) is a common postoperative complication after extubation with an incidence of 14–62% [1–3]. POST refers to the throat pain caused by irritation or damage to the mucosa or airway structures due to airway manipulation or the airway device itself. Previous systematic reviews show that factors such as female sex, high cuff pressure, and inappropriately sized tube are associated with POST [3, 4]. However, there is as yet no clear evidence to point out the main cause of POST. Therefore, the principle goal of the current researches is to identify the main influencing factor so as to effectively intervene and prevent POST.

Some studies suggest that high cuff pressure of the endotracheal tube may be a vital contributing factor [5, 6]. The ideal cuff pressure is one that does not affect the blood perfusion of tracheal mucosa, achieves no airway leakage during ventilation, and prevents ventilator-associated pneumonia (VAP) due to the aspiration of subglottic secretions. Accordingly, it is recommended to maintain cuff pressure in the range of 25–30 cmH_2_O (18–22 mmHg) after inflation, lower than the capillary perfusion pressure of the tracheal mucosa [7, 8]. At present, two methods are commonly used to monitor cuff pressure in clinical practice. Many anesthesiologists prefer the pilot balloon palpation method to estimate the cuff pressure despite the risk of endotracheal cuff overinflation [9]. Most respiratory physicians’ choice to measure cuff pressure is an endotracheal cuff pressure manometer. Although the manometer is accurate to measure cuff pressure, manual intermittent measurement and close observation are required. Each time the manometer is connected to the pilot balloon and then separated, there is a drop in cuff pressure of 2–3 cmH_2_O [10]. Moreover, a pressure transducer has been reported in studies [11–13] as a better method to measure cuff pressure than the two mentioned above.

Cuff pressure measurement by the manometer can reduce the incidence of POST in patients scheduled for gynecological laparoscopic surgery [14]. However, no studies have yet investigated the different effects of pressure transducer-guided cuff pressure measurement with or without adjustment on POST in patients undergoing gynecological laparoscopic surgery.

## Objectives

The aim of this study is to confirm whether continuous measurement of endotracheal tube cuff pressure and maintaining it at the normal value (18–22 mmHg) compared with only continuous measurement without adjustment could effectively reduce the incidence of POST in patients undergoing gynecological laparoscopic surgery.

## Methods

### Study design

This is a single-center, parallel-group, randomized controlled, superiority trial with a 1:1 allocation ratio. The time schedule of the protocol (Table 1) is based on the Standard Protocol Items: Recommendations for Interventional Trials (SPIRIT) 2013 [15].

**Table 1 Tab1:** The schedule of enrollment, interventions, and assessments

	Study period			
	Enrollment	Allocation	Post-allocation (post-extubation)	
Time point	− 1 day before surgery	Day of surgery	0 h	24 h
Enrollment				
Eligibility screen	X			
Informed consent	X			
Allocation		X		
Interventions				
CPMA group		X		
Control group		X		
Assessments				
Baseline variables	X	X		
Number of patients with POST at rest			X	X
Number of patients with cough			X	X
Number of patients with hoarseness			X	X
Number of patients with PONV			X	X
Pain intensity (NRS)			X	X

### Study setting

This randomized controlled study will be performed at Beijing Chaoyang Hospital, Capital Medical University, Beijing, China.

### Study population

#### Inclusion criteria

Patients scheduled for elective gynecological laparoscopic surgery under general anesthesia will be recruited. Participants with ages between 18 and 65 years, body mass index (BMI) of 18–30 kg/m^2^, and American Society of Anesthesiologists (ASA) classes I–II must voluntarily sign a written informed consent before the intervention.

#### Exclusion criteria

Patients will not be eligible with one of the following criteria: preoperative cough, sore throat, or upper respiratory tract infection; preoperative nasogastric tube insertion; smoking history; history of nausea and vomiting; history of oropharynx and larynx surgery; or other conditions that will interfere with the benefits of patients in the trial identified by researchers.

### Interventions

No preoperative medication will be used in all patients. After entering the operating room, patients will be routinely monitored for non-invasive arterial blood pressure, electrocardiogram, pulse oxygen saturation, end-tidal carbon dioxide, and then inhale oxygen through a mask. After peripheral venous catheterization, midazolam (0.02–0.05 mg/kg), sufentanil (0.2–0.5 μg/kg), propofol (2–3 mg/kg), and rocuronium (0.6–0.8 mg/kg) will be injected intravenously during induction of general anesthesia. The anesthesiologists with at least two years of experience will select polyvinyl chloride endotracheal tubes of 7.0 mm internal diameter for video laryngoscope-guided intubation. In the cuff pressure measurement and adjustment (CPMA) group, the anesthesiologist will connect the pressure transducer to the spring-loaded one-way valve of the pilot balloon through a three-way connector and then inflate or deflate the tube cuff with a syringe connected to a tee-junction to maintain 18–22 mmHg cuff pressure intraoperatively. In the control group, the tube cuff pressure will be adjusted by anesthesiologists’ experience with pilot balloon finger palpation before the operation and will not be adjusted during the operation but will be monitored blindly on the portable monitor which screen will be fully covered. The number of tracheal intubation attempts, cricoid compression, and cough during intubation will be recorded. After successful endotracheal intubation, volume-controlled ventilation will be performed with a tidal volume of 6–8 ml/kg, a respiratory rate of 12–18 breaths per minute, an inspiratory-to-expiratory ratio of 1:2, an inspired oxygen fraction of 80%, and a flow rate of 1–2 L/min to adjust end-expiratory carbon dioxide partial pressure to 35–45 mmHg. Total intravenous anesthesia will be maintained with propofol (4–6 mg/kg/h) and remifentanil (0.1–0.25 μg/kg/min). Additional rocuronium 10–20 mg and sufentanil 5–10 μg will be administered as needed during the operation. After the establishment of carbon dioxide pneumoperitoneum, the patients in both groups will be placed in the Trendelenburg position required for gynecological laparoscopic surgery. The pneumoperitoneum pressure will be kept at 14 mmHg. Hemodynamic changes will be monitored and recorded every 5 min during the operation. Operation time and endotracheal tube indwelling time will also be recorded. After the surgery, gentle suction of oropharyngeal secretions will be performed in both groups (the wall suction pressure ranges from − 80 to − 120 mmHg). The administration of intravenous muscle relaxant antagonist (neostigmine 40 μg/kg) will be determined based on the assessment of muscle strength recovery. Once the patient is fully awake, the tidal volume has been restored to normal, and sufficient oxygen saturation can be maintained, air will be withdrawn from the cuff, and the endotracheal tube will be removed. In addition, the number of coughs before extubation will be recorded. Both groups of subjects will receive postoperative pain control via an analgesic pump with sufentanil at a rate of 2 μg/h and a total dose of 100 μg. Sore throat at rest and its severity, cough, hoarseness, nausea and vomiting, and pain score will be recorded immediately after extubation (0 h after extubation) and within 24 h after extubation. The investigators will record conditions in which enrolled subjects are deemed unfit to proceed with the study due to the following reasons: occurrence of adverse events, including severe adverse events, and other circumstances identified by the researchers as unsuitable for further experimentation. To enhance participants’ adherence with the intervention measures, researchers will employ clear and comprehensible language to communicate with patients, conduct timely follow-ups, and engage in interactive discussions. The researchers will also record timely during the intervention and follow-up process to monitor the compliance of the subjects.

### Outcomes and measurements

#### Primary outcome

The primary outcome is the incidence of sore throat at rest within 24 h after extubation. The total number of patients with sore throat at rest between two assessment time points (0 h and 24 h post-extubation) will be recorded.

#### Secondary outcomes

The secondary outcomes include the following: (1) the incidence of cough within 24 h after extubation; (2) the incidence of hoarseness within 24 h after extubation; (3) the incidence of PONV within 24 h after extubation; (4) the intensity of POST within 24 h after extubation graded on a 0–3 scale: 0 = no sore throat, 1 = mild sore throat (less pain than a cold), 2 = moderate sore throat (like a cold), and 3 = severe sore throat (more severe than a cold) [16–19]; and (5) 11-point Numerical Rating Scale (NRS) for pain intensity within 24 h after extubation: 0 = no pain and 10 = worst pain imaginable [20].

### Sample size calculation

The sample size estimation is based on the incidence of sore throat while resting within 24 h post-extubation. This superiority trial with a 1:1 allocation ratio will achieve 80% power (1 − β) and a one-sided significance level (*α*) of 0.025. In a randomized controlled study of gynecologic laparoscopic surgery [14], the incidence of POST was 31.7% (19/60) in cuff pressure adjusted to 25 cmH_2_O group (using the manometer) and 68.3% (41/60) in the control group (using palpation of the pilot balloon). Based on this study of a similar surgery, we estimate the incidence of sore throat at rest within 24 h post-extubation is 32% in the CPMA group and 68% in the control group. Then, 54 participants should be needed according to the conditions mentioned above. Eventually, a total of 60 patients (30 in each group) will be recruited so as to allow for a 10% dropout rate. The sample size was calculated using tests for two proportions in the PASS software (version 15, NCSS Corp., USA).

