### Statistical analyses

All data will be analyzed by the SPSS software (version 26, IBM Corp., USA). Both the intention-to-treat analysis and the per-protocol analysis will be performed for the primary outcome. Subgroup analyses will be performed based on the values of the incidence of cough, hoarseness, and PONV; the intensity of POST; and NRS for pain intensity within 24 h after extubation. A two-sided significance level will be set at *P* < 0.05 for all statistical tests. The continuous variables will be expressed as a mean with standard deviation (normal distribution) or a median with interquartile range (skewed distribution). Student’s *t* test will be used to compare normally distributed continuous variables, and the Mann–Whitney *U* test will be used to compare non-normally distributed continuous variables. The categorical variables such as the incidence of sore throat, cough, hoarseness, and PONV within 24 h after extubation will be described as counts and percentages. Differences between the groups of these categorical variables will be compared with *χ*^2^ analysis or Fisher’s exact test. The missing data will be handled by multiple imputation.

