## Discussion

POST may be disappearing within 48 h in most cases, but it is not conducive to the postoperative comfort of patients. If it is not taken seriously, patients who have retained the endotracheal tube for a long time (such as patients in intensive care units) may have more serious complications than POST, such as tracheomalacia, laryngotracheal stenosis, and tracheoesophageal fistula. This is a parallel-group, randomized controlled, superiority trial with a robust methodology to confirm whether maintaining intraoperative endotracheal tube cuff pressure below the tracheal capillary perfusion pressure could effectively reduce the incidence of POST in patients undergoing gynecological laparoscopic surgery. The method of using a pressure transducer to measure cuff pressure continuously is more convenient and accurate than a cuff pressure manometer. This trial’s methodological strengths include Internet central randomization, computer-generated assignment, allocation concealment, blinded assessment, and appropriate estimation of sample size. Considering this is a single-center study, the conclusion might not be generalizable. The result of this study could be used as a reference for future multicenter studies to confirm the effect of cuff pressure on POST and provides a scientific theoretical basis for preventing POST to further support comfort medicine.

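### The 80% power stated for 54 evaluable patients does not hold for the planned χ² test, which has about 75% there and needs all 60

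*Protocol article*

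**What the plan says.** Protocol article, Sample size calculation: "This superiority trial with a 1:1 allocation ratio will achieve 80% power" at a "one-sided significance level" of 0.025. The assumed incidence of sore throat at rest within 24 h "is 32% in the CPMA group and 68% in the control group", taken from an earlier trial in similar surgery (19/60 and 41/60). The result is "Then, 54 participants should be needed according to the conditions mentioned above", raised to 60 (30 per group) for 10% dropout. The software procedure is given as tests for two proportions in PASS, without the test statistic.

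Protocol article, Statistical analyses: "A two-sided significance level will be set at" 0.05. For a list of categorical outcomes that includes sore throat, "Differences between the groups of these categorical variables will be compared with" χ² or Fisher's exact test. The primary outcome is analysed by intention to treat and per protocol, with multiple imputation for missing data.

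Protocol article, Discussion: "appropriate estimation of sample size" is listed among the methodological strengths.

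**The concern.** A sample size carries its stated power only for the test it was computed for. At these rates the variance under the alternative is smaller than the pooled variance that Pearson χ² uses under the null. An unpooled formula therefore asks for fewer patients than χ² needs. If 54 came from the unpooled form, the number the plan treats as sufficient after dropout does not give χ² its 80%. At stake is a power figure, offered as a design strength, that a reader would use to judge a non-significant result.

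**Working it through.** **Inputs** (Sample size calculation): p₁ = 0.32, p₂ = 0.68, difference 0.36, "1:1 allocation ratio", one-sided α 0.025 (z = 1.960), power 80% (z = 0.842). Two-sided 0.05 in Statistical analyses has the same upper critical value, so sidedness changes nothing below.

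**Reproducing 54.** Unpooled Z formula:

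n per arm = (1.960 + 0.842)² × (0.32×0.68 + 0.68×0.32) / 0.36² = 26.36, so 27 per arm and 54 in total. Dropout: 54/0.9 = 60. Both stated figures are reproduced.

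**Other standard variants at the same inputs:** arcsine 28.94 (29 per arm, 58); continuity-corrected 35 per arm (70); pooled as below (60). None gives 54.

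**Sizing for χ².** With mean rate 0.5, the pooled formula is

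n per arm = (1.960×√0.5 + 0.842×√0.4352)² / 0.36² = 29.07, so 30 per arm and 60 evaluable. Keeping a 10% allowance would mean 60/0.9 = 66.7, so 67 enrolled.

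**Power at 27 per arm, normal approximation.**
- Unpooled: Φ(0.36×√27/√0.4352 − 1.960) = Φ(0.876) = 80.9%.
- Pooled: Φ((0.36×√27 − 1.960×√0.5)/√0.4352) = Φ(0.735) = 76.9%.

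**Exact power**, summing the two binomial distributions over every table the test rejects at two-sided 0.05:

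| Per arm | Evaluable | χ² (uncorrected) | Fisher |
|---|---|---|---|
| 27 | 54 | 74.8% | 65.3% |
| 28 | 56 | 77.4% | 68.4% |
| 29 | 58 | 79.8% | 71.2% |
| 30 | 60 | 82.0% | 74.1% |

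**Which column applies.** At 27 per arm and 50% overall incidence, expected cell counts are 27 × 0.5 = 13.5, far above the usual threshold of 5. By that convention χ² would be used for the primary outcome.

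**Sensitivity to the borrowed rates.** The binomial standard error of 19/60 is √(0.317×0.683/60) = 0.060. Moving the control rate by that amount, with 0.32 held fixed, exact χ² power at 27 per arm is 58.1% at 62% and 87.9% at 74%.

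**The case against.** Four points on the other side have force.

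- **The number is right by its own formula.** 54 and 60 both follow from the stated inputs. A reader might infer a calculation error. The article does not support that; what is wrong is the pairing with the later test. The unpooled form itself is inferred. The power of χ² at 54 does not depend on that inference.
- **Fisher is unlikely to be used for the primary outcome.** A reader might take 65% as the trial's power, or call the χ²-or-Fisher wording a defect. The wording covers a list of outcomes, some of which may be rare, and the rule for choosing may sit in an analysis plan not shown here. The Fisher figures apply only if that test is actually chosen.
- **Loss may be small.** Follow-up ends 24 h after extubation, the Data collection and management section commits to completing follow-up for those who drop out or deviate, and the intention-to-treat analysis keeps deviators with observed outcomes. A reader might infer that the trial is underpowered as enrolled. With all 60 evaluable it is not: χ² has 82.0%. But the plan itself budgets for 10% loss, and multiple imputation recovers little about outcomes never observed.
- **The borrowed rates matter more.** One standard error in the control rate moves power by 13 to 17 points, against 5 here. That limits the weight of the point but does not make the stated figure correct at the stated rates.

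**Conclusion.** The concern holds in limited form, at moderate weight. At the article's own rates and its own 10% loss, the planned χ² test has about 75% power (exact 74.8%; pooled approximation 76.9%), not 80%. It reaches 80% at 30 per arm, so the 60 enrolled suffice only with essentially no loss, and the dropout allowance is in effect used up. If Fisher were used, power would be about 65% at 54 and 74% at 60. This rests on 32% against 68%, equal arms, an uncorrected χ² at two-sided 0.05, and loss meaning that the outcome is not observed. Type I error and bias are not affected by the shortfall.

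**What to change.** In the sample size section, state which test statistic produced 54. Name uncorrected Pearson χ² as the primary test, with Fisher only if an expected count is below 5, and record this before unblinding. Restate power as about 82% with 60 evaluable patients and about 75% with 54. Qualify "appropriate estimation of sample size" in the Discussion to match.

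This costs some wording and a slightly less favourable power figure. It needs no extra patients. Switching the analysis to an unpooled Z test to match the sizing would be a poor alternative: at 27 per arm its exact two-sided type I error is 5.9% to 7.6% for common rates of 30% to 50%, against 4.2% to 5.4% for χ².

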### Recruitment

The recruitment process will be simplified. Unnecessary application documents and requirements will be reduced. Emphasizing the significance and benefits of the study is crucial to stimulate the interest and willingness to participate among potential participants.

### Assignment of interventions

#### Randomization

Participants will be randomly assigned to either the CPMA or the control group with a 1:1 allocation on the day of surgery using Ericure, which is a computer-generated central randomization online service [21]. Blocked randomization using permuted blocks of random sizes will reduce the predictability of the allocation sequence. The allocation sequence in the central randomization system will be managed by a statistician independent of the research. Blinded study personnel who are unaware of the allocation sequence will receive a randomization code via a central randomization system on the day of surgery, following subject screening and all baseline measurements, thereby ensuring allocation concealment. The allocation sequence will be concealed without the influence of selection bias until the completion of the database analysis.

#### Blinding

As a result of the different types of intervention, neither anesthetists nor gynecologists will be blinded to the allocation. However, the patients, the data collectors, the outcome assessors, and the statistician will be masked to the information about the allocation. For example, an observer who is unaware of the allocation will assess for sore throat of the patients within 24 h after extubation. Unblinding will be performed after the completion of the database analysis. If a serious adverse event occurs in the participant, the principal investigator will log into the central randomization system for emergency unblinding.

### Data collection and management

Clinical data of the patients will be collected by trained researchers who are unaware of the group assignment. All clinical trial data will be recorded using an electronical case report form (eCRF). After the data monitoring staff verifies the accuracy and completeness of the source document, the data entry personnel will establish the database with the EpiData software (version 3.1, EpiData Association, Denmark). For any subjects who drop out of or deviate from the trial for any reason, the reasons will be recorded as thoroughly as possible. Prompt and appropriate measures will be taken to address or treat their withdrawal, ensuring completion of follow-up and reporting of all observed outcomes. After logical range checks for data values, the database with independent double data entry will be locked and backed up.

